**Methods/design:**

We describe an ongoing parallel, two-armed, non-inferiority randomised controlled trial that compares routine and teledental pathway of dental care in children aged 4–15 years (*n* = 250). Participating schools in Western Australia will be randomly assigned to the control or teledental group, approximately three schools in each group with a maximum of 45 children in each school. All participants will first receive a standard dental examination to identify those who require urgent referrals and then their teeth will be photographed using a smartphone camera. At the baseline, children in the control group will receive screening results and advice on the pathway of dental care based on the visual dental screening while children in the teledental group will receive screening results based on the assessment of dental images. At 9 months follow-up, all participants will undergo a final visual dental screening. The primary outcomes include decay experience and proportion of children become caries active. The secondary outcomes include the diagnostic performance of photographic dental assessment and costs comparison of two pathways of dental care.

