The proposed project builds on previous validation trials that examined the feasibility of the teledentistry approach to dental screening [25–27]. The findings showed that the use of dental photography in dental screening is feasible and offered a moderate diagnostic accuracy relative to visual dental screening. Recent systematic reviews indicated that most reviewed studies concerned with teledental diagnosis demonstrated comparable results between photographic and visual inspection techniques [28, 29]. Although telehealth applications are becoming increasingly popular in dentistry, controlled assessments of clinical outcomes, long-term use and economic analyses of teledentistry are still limited [30–32]. A comparison of the costs of teledentistry and its alternatives is of great importance to those making future decisions about implementing a new service. In this study, we propose a paradigm shift in the existing dental services through role substitution and taking advantage of user-friendly mobile technology and the widely available Internet to improve school children access to dental services.

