#### Follow up

At 9 months following the baseline dental assessments, all participants will be invited to undergo a standard visual dental check-up to assess the dental status, determine if treatment was received and see whether parents adhere to the recommendations received at the baseline.

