### Outcome assessment

*Primary outcomes* include decay experience in either dentition as measured by the DFT/dft (decay, filled teeth) index at the baseline and 9-month follow up. Teeth will be classified as carious if have arrested caries, caries into dentine or enamel level caries. In addition to the proportion of children becomes caries-active at the 9-month follow-up which refers to the percentage of children developing one or more new caries in any of the previously caries-free teeth when assessed at the baseline. Data will be collected from one of our system’s functional components running on the backend to automatically record dental assessments based on dental images and through the oral health assessment forms completed by OHTs in the control group.

*Secondary outcomes* include the diagnostic performance of photographic dental assessment versus standard dental examination at the baseline. The participants’ dental care utilisation patterns collected via a baseline survey (Additional file 2) and adapted from Kopycka-Kedzierawski et al. [36]. Also, costs comparison between the two pathways of dental care will be conducted to identify the least costly alternative. The resources for the usual pathway of dental care will include vehicle costs, admin costs (e.g. telephone appointments, printing services and postage) and costs of consumables used in visual dental screening and the dental practitioner’s time. The resources for the teledental pathway of dental care include: software licence fees, ICT equipment, Internet and software engineer’s time, admin costs (e.g. telephone appointments, printing services and postage), costs of consumables used in dental photography, tele-assistants (photographer) time, and offsite dental practitioners’ time for reviewing dental images. Dental care costs for all children include the following: restorations, restorations with crowns and extractions. The costing data will be based on those incurred by the health system and will be derived from a survey and web-based open-access sources [37].

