### Data analysis

The sensitivity and specificity values for the photographic caries assessment will be estimated and compared to the reference visual dental assessment at the baseline. Kappa statistic will be used to estimate the inter-rater reliability of the photographic dental assessments by two independent OHTs. 15% of dental images will be re-examined to test intra-rater reliability at least, 4 weeks after the initial review of images.

The baseline data will be used to generate descriptive statistics for the intervention and control groups (teledental versus usual care pathway). General linear regression models will be performed to compare the efficacy of the interventions on decay (mean DFT/dft) between intervention and control groups, adjusting for baseline data collected via a survey that includes tooth brushing (yes/no; frequency); dental visit patterns over the past year, child age, Indigenous status, Socio-Economic Indexes for Areas (SEIFA), private insurance status and educational level of parents. The measure of intervention efficacy will be the difference between the intervention and control groups in adjusted DFT/dft (caries incidence) per child. All analyses will be performed using SAS (version 9.4). In addition, a cost minimisation analysis will be undertaken to compare the costs associated with teledental versus the usual pathway of dental care over 9 months. This will include both the cost of the initial screening, and any subsequent interventions occurring over the 9 months. The analysis will be conducted from the perspective of the health system and, will not take into consideration the costs incurred by the families. All salaries used in the calculation will be based on Australian government rates and will include on-costs.

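### As written, the primary-outcome data sources give the teledental arm a photographic baseline and the control arm a visual one, so lesions missed on photographs can count as new caries in one arm only

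*Protocol article*

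**What the plan says.** The Outcome assessment section of the protocol article sets two primary outcomes. The first is decay experience, the "DFT/dft (decay, filled teeth) index at the baseline and 9-month follow up". The second is the proportion of children who become caries-active, defined as "the percentage of children developing one or more new caries in any of the previously caries-free teeth when assessed at the baseline". The threshold is low: "Teeth will be classified as carious if have arrested caries, caries into dentine or enamel level caries".

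The same paragraph closes with the data source. A backend component of the system will "automatically record dental assessments based on dental images and through the oral health assessment forms completed by OHTs in the control group". The forms are tied to the control group, and nothing visual is named for the teledental group.

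The follow-up method is the same for everyone. The abstract states: "At 9 months follow-up, all participants will undergo a final visual dental screening". The Follow up section agrees that "all participants will be invited to undergo a standard visual dental check-up to assess the dental status".

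Three other places show that a visual baseline exists for every child. The abstract has all participants examined before they are photographed. The section on the visual dental examination records the findings on the assessment form and limits to controls only the sending of those results to parents. Data analysis uses the baseline visual assessment as the reference for sensitivity and specificity.

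**The concern.** The caries-active outcome depends on the baseline status of each tooth. If that status comes from photographs in one arm and from a visual examination in the other, with a visual examination for all at 9 months, the arms differ in how they are measured as well as in the care they receive. A carious tooth that the photograph misses enters the at-risk set as sound. When the visual examination finds it at 9 months, it counts as new disease. This route is open only in the teledental arm.

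Misses are to be expected. The Background says that the photographic approach in earlier studies "offered a moderate diagnostic accuracy relative to visual dental screening", and enamel-level lesions count as caries here. The trial is a non-inferiority comparison, so an artefact of this kind could make an equally effective teledental pathway look worse. Its size would depend on the diagnostic error that the trial's third objective sets out to estimate.

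**Working it through.** **Sources by arm and visit, following the Outcome assessment sentence together with the Follow up section**

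| | Baseline | 9 months |
|---|---|---|
| Teledental | image-based record | visual |
| Control | visual form | visual |

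The sentence cannot describe both visits, because image-based teledental data at 9 months would contradict the visual follow-up of all participants. Baseline is the only visit at which it can apply to that arm.

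**Inputs from the documents**
- Caries prevalence 35% (Sample size calculation). The plan's figures reproduce: 1.96² × 0.90 × 0.10 / 0.10² = 34.57, so 35 children with caries; 35 × 1.86 = 65.1, so 65 without; 100 / 0.80 = 125 per group.

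**Assumptions, not in the documents**
- True 9-month incidence p0 is equal in both arms: 20%, varied from 10% to 30%.
- Tooth-level photographic sensitivity s is 0.90, 0.80 or 0.70.
- Affected children have k = 1 or 3 carious teeth.
- Misses are independent between teeth, there are no photographic false positives, and every missed lesion is recorded at 9 months.

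**Caries-active outcome**

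The chance that at least one carious tooth is missed in an affected child is 1 − s^k. Only children who are not truly caries-active can be added falsely, so:

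false excess = (1 − p0) × 0.35 × (1 − s^k)

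With p0 = 0.20 the multiplier is 0.80 × 0.35 = 0.28.

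| s | k = 1 | k = 3 |
|---|---|---|
| 0.90 | 0.28 × 0.100 = 2.8 points | 0.28 × 0.271 = 7.6 points |
| 0.80 | 0.28 × 0.200 = 5.6 points | 0.28 × 0.488 = 13.7 points |
| 0.70 | 0.28 × 0.300 = 8.4 points | 0.28 × 0.657 = 18.4 points |

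With p0 from 10% to 30% and s down to 0.60, the extremes are 0.70 × 0.35 × 0.100 = 2.45 points and 0.90 × 0.35 × 0.784 = 24.7 points.

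A false positive works the other way by removing a sound tooth from the at-risk set. At an assumed 1% per tooth, with one new lesion per truly active child, it hides about 0.20 × 0.01 = 0.2 points, which is small beside every entry in the table.

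**DFT/dft, only if change from baseline is analysed**

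Spurious increment from misses = 0.35 × k × (1 − s).
- k = 1: 0.035, 0.07 and 0.105 teeth per child at s = 0.90, 0.80 and 0.70.
- k = 3: 0.105, 0.21 and 0.315.

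False positives subtract. An assumed 1% over about 22 sound teeth gives 22 × 0.01 = 0.22. At s = 0.80 and k = 3 the net is 0.21 − 0.22 = −0.01, so the sign is not fixed. If 9-month visual DFT/dft is compared without a baseline value, both arms are measured alike and this error is zero.

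**With the visual baseline used in both arms**, the artefact from photographic misses is zero for both outcomes, and the sample size stays at 125 per group.

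I give no probability of a falsely significant result. Allocation is by school, and the article gives no intraclass correlation with which to allow for it.

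**The case against.** The strongest reply is that this is a loose sentence rather than a design decision. It does not mention baseline and does not say that the image records belong to the teledental group. All children are photographed, so image records exist for controls too. It could be a list of the two capture systems, electronic and paper. The visual baseline is recorded for every child and already serves as the diagnostic reference, so the investigators may well intend to use it.

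Much of this stands. A reader might infer that the protocol has deliberately chosen a photographic outcome baseline for the teledental arm; the text is too imprecise to show that. But the sentence closes the primary-outcome paragraph, ties the forms to controls and names no visual source for the other arm. An analyst who followed it would use the image data. That the visual baseline exists shows that the problem can be repaired, not that the plan has avoided it.

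A reader might also infer that DFT/dft is biased against the teledental pathway. The documents do not support that. The regression described under Data analysis specifies no change score. Only the label in "the difference between the intervention and control groups in adjusted DFT/dft (caries incidence) per child" points to an increment, and even then false positives can cancel or reverse the effect.

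Finally, a reader might take 0.35 × (1 − s³), which is 9.5%, 17% and 23% at sensitivities of 0.90, 0.80 and 0.70, as the share of teledental children falsely called caries-active. That overstates it, because some of these children have genuinely new caries and would be counted anyway. It also shows only the three-tooth case.

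**Conclusion.** The point holds for the caries-active co-primary outcome, on the plain reading of the data-source sentence. Followed as written, that outcome is photograph-to-visual in the teledental arm and visual-to-visual in the control arm, and missed lesions bias it against the teledental pathway. At 35% prevalence and an assumed 20% true incidence in both arms, the false excess is about 2.8 to 8.4 percentage points with one carious tooth per affected child, and about 7.6 to 18.4 with three, for sensitivity from 0.90 down to 0.70.

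Only the prevalence comes from the protocol. Sensitivity, incidence, number of carious teeth and independence of misses are assumed. So is the recording of every missed lesion at follow-up; teeth shed in the meantime would lower the figures. The range is therefore an illustration, not an estimate. For DFT/dft the point is conditional on an analysis of change, and no direction can be claimed. The correction should be made before analysis, because a differential measurement error in a co-primary outcome can be removed by wording alone.

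**What to change.** In Outcome assessment, replace the data-source sentence with a statement that DFT/dft and caries-active status, at baseline and at 9 months, are taken from the OHT visual examination in both arms. Add that image chartings are used only to prepare the advice sent to teledental families and for the diagnostic-accuracy objective.

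The cost is a change of wording, plus a check that the baseline visual forms of the teledental children are entered in the outcome data set. The examinations are already planned for every child at both visits, so none are added and the sample size does not change. The article reports that data collection is still under way, so the change can be made before analysis.

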### Sample size calculation

The sample size calculation is based on a two-sided 95% CI for a single proportion using the Z-test approximation, an effect size of 0.1 and an expected observed proportion of 0.90. The number of participants with caries that meet the power of 0.8 is estimated to be 35 [n ≥ (Z^2^/m^2^) p (1 - p)]. With the prevalence of caries at 35% (1.86 × 65), 65 participants without caries are needed. After considering a 20% drop out rate, the proportion that gives the largest sample size shows that at least 125 children per group will be needed. Three schools will be required in each group with a maximum of 45 children in each school.

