## Methods

This community-based project is a parallel, two-armed, non-inferiority randomised controlled trial (RCT) that seeks to determine the efficacy and net economic benefits of using telehealth to facilitate dental care delivery within school settings and aid in generating data which will assist to leverage the planning and justification for a multicentre large RCT. The study will be conducted in accordance with the SPIRIT Statement for reporting a clinical trial protocol [33] (checklist provided as Additional file 1).

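### The sample size formula contains no power term and sizes a secondary diagnostic outcome, so no power is shown for the primary non-inferiority comparison

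*Protocol article*

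**What the plan says.** All of this is in the protocol article.

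- **Sample size calculation, basis:** "The sample size calculation is based on a two-sided 95% CI for a single proportion using the Z-test approximation", with "an effect size of 0.1 and an expected observed proportion of 0.90". The formula printed is n ≥ (Z²/m²) p(1 − p).
- **Sample size calculation, power:** "The number of participants with caries that meet the power of 0.8 is estimated to be 35".
- **Sample size calculation, children without caries:** "With the prevalence of caries at 35% (1.86 × 65), 65 participants without caries are needed".
- **Sample size calculation, arm size:** after a 20% allowance for dropout, "at least 125 children per group will be needed". On schools: "Three schools will be required in each group with a maximum of 45 children in each school".
- **Methods and Abstract:** the trial is a two-arm non-inferiority randomised trial with 250 children. Every child is both examined and photographed.
- **Outcome assessment:** the primary outcomes are DFT/dft and the proportion becoming caries-active at 9 months. Diagnostic performance at baseline is secondary.
- **Allocation:** the school is named as the unit of allocation. The same paragraph also describes permuted blocks of 4 at each school, with lists opened as participants are enrolled.

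**The concern.** The section attaches a power of 0.8 to a formula that cannot deliver any specified power, because it has no term for the type II error. It also serves as the only justification for the size of a two-arm trial, although what it sizes is a single proportion in one cohort.

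At stake is how the main result is read. If the arms do not differ, a reader who sees 0.8 beside the arm size may take that as evidence of non-inferiority from an adequately powered trial. Nothing in the calculation bears on that comparison.

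**Working it through.** **1. Reproducing the plan's figures.** Inputs from the sample size section: Z = 1.96 (two-sided 95%), p = 0.90, m = 0.10, prevalence 35%, dropout 20%.

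- With caries: 1.96² × 0.90 × 0.10 / 0.10² = 34.57, rounded up to 35.
- Total: 35 / 0.35 = 100, so 65 without caries.
- With dropout: 100 / 0.80 = 125.

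All three figures match, and 0.8 as a power is never used. (The 0.80 in the last step is the retention rate.)

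**2. Does any power-bearing version give 35?** Adding a power term, (1.96 + 0.84)² × 0.09 / 0.01 gives 71 two-sided. The one-sided version gives 56. Testing 0.90 against a null of 0.80 with the null variance gives 108 two-sided or 83 one-sided. The protocol states no such null; it is assumed here only for the check. None of the four gives 35.

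**3. The printed product.** 1.86 × 65 = 120.9, whereas 1.86 × 35 = 65.1. The second factor is a slip for 35. N does not change.

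**4. What the number sizes.** Counts with and without the condition are the denominators of sensitivity and specificity. The section does not use those words, but no other reading fits, and Data analysis plans exactly those estimates. As every child has both assessments, 100 (or 125) is the total for one cohort. The section assigns it to each group.

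**5. Diagnostic precision at the planned enrolment.** Accuracy is assessed at baseline on all 250 children: 250 × 0.35 = 87.5, about 88 with caries. The expected half-width is 1.96 × √(0.09/88) = 0.063. At true sensitivity 0.90, the chance that the half-width is at most 0.10 is above 99.9% with 88 children with caries, against 53% with 35. This ignores correlation within schools.

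**6. Illustration for a primary outcome.** The following are assumptions, not in the protocol: 30% caries-active in both arms, a 10-point margin, one-sided 2.5%, and ICC 0.01 to 0.05. The 100 completers per arm are 125 less 20%, or about 33.3 per school with three schools.

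- SE without clustering: √(2 × 0.30 × 0.70 / 100) = 0.0648.
- Design effect: 1 + (33.3 − 1) × ICC, which is 1.32 at ICC 0.01 and 2.62 at ICC 0.05. The SE becomes 0.0746 and 0.1048.
- Power by normal quantiles: Φ(0.10/SE − 1.96).
- Power on 4 df (six schools less two): noncentral t with critical value 2.776.

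| | No clustering | ICC 0.01 | ICC 0.05 |
|---|---|---|---|
| Power, normal | 34% | 27% | 16% |
| Power, 4 df | 22% | 18% | 11% |
| 95% CI half-width, normal (1.96 × SE) | 12.7 points | 14.6 points | 20.5 points |
| 95% CI half-width, 4 df (2.776 × SE) | 18.0 points | 20.7 points | 29.1 points |

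The rows should be read across. Comparing a normal figure with a 4-df figure mixes the effect of clustering with that of the reference distribution.

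The event rate matters, but 80% is not reached in the range tried. Unclustered normal power at the 10-point margin is 65%, 42% and 32% at event rates of 10%, 20% and 35%.

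**The case against.** A good deal can be said for the plan.

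- **The arithmetic of N is right.** 125 follows from the stated inputs, and the 1.86 slip has no consequence. This stands.
- **Diagnostic accuracy is well served.** A reader might infer that 35 children with caries leave the diagnostic aim short, or that the trial is adequate for nothing. The protocol does not support that: both arms contribute at baseline, and about 88 children with caries comfortably meet the 0.10 precision.
- **The 0.8 is attached to the number with caries.** A reader might infer that the protocol claims 80% power for non-inferiority. It does not say so. What stands is that the figure is wrong where it is placed and that no power is shown for the primary comparison.
- **The Methods section says the trial will help plan a larger one.** That would justify a size set for estimation. The same section also sets out to determine efficacy, and the first hypothesis is that the teledental pathway is as effective as routine care. The sample size section does not present the comparison as estimation only.
- **A condensed article may leave the margin and ICC to a fuller document.** Agreed; their absence is not the point. The article itself prints the formula and the power statement, and the two conflict.
- **The clustered figures depend on school allocation.** Allocation states this but contradicts it with blocks of 4 at each school. If children were allocated within schools, the design effects and the 4-df figures would not apply. The missing power term, the secondary target and the unclustered 34% do not depend on this.

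**Conclusion.** The point holds. The formula fixes the precision of one proportion and has no power term, so the statement that 35 children with caries give a power of 0.8 is wrong as written. The resulting one-cohort total, for a secondary outcome, is used as the arm size of a non-inferiority trial. The calculation therefore says nothing about either primary outcome. These conclusions need no outside figures.

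The size of the gap for the primary comparison can only be illustrated. Under the assumptions in step 6, power is 34% unclustered and 27% to 16% clustered by normal quantiles, or 22% and 18% to 11% on 4 df. These figures do not measure a shortfall against a margin the protocol states. The clustered ones also presume that schools are the unit of allocation, with about three per arm.

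**What to change.** In the sample size section:

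1. Label the existing calculation as precision for diagnostic accuracy (100 evaluable children in one cohort), and note that both arms contribute at baseline.
2. Delete the statement that 35 children with caries give a power of 0.8.
3. Correct the printed product to 1.86 × 35 (minor; N unchanged).
4. Add a separate statement for the primary between-arm comparison. Give the achievable CI half-width or power with about three schools per arm and about 33 completers per school, over a stated ICC range and with the few degrees of freedom that six schools allow.
5. Describe that comparison as estimation to inform the larger trial mentioned in Methods.

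The two descriptions of randomisation under Allocation should be reconciled first, because they decide whether the clustered calculation applies.

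The cost is a text change with no extra children. The downside is that the stated power becomes less favourable.
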